## STUDY ABSTRACT

### TITLE

Phase II Double-blinded Randomized Controlled Evaluation of MVA85A/AERAS-485 for Safety, Immunogenicity and Prevention of Tuberculosis in BCG-Vaccinated, HIV-negative Infants

### RATIONALE

The available live tuberculosis vaccine, BCG provides incomplete protection against pulmonary tuberculosis. Due to natural inhibition of a second dose, a BCG revaccination does not provide much additional protection. MVA85A/AERAS-485 presents a tuberculosis antigen in the setting of a live but non-replicating virus vaccine to increase T-cell immunity and thus protection against tuberculosis. MVA85A/AERAS-485 has been administered to over 300 humans without any vaccine-related serious adverse effects and shows evidence of immunogenicity. This study will evaluate the safety and immunogenicity of MVA85A/AERAS-485 in BCG vaccinated infants and has the potential to demonstrate the ability of the vaccine to prevent tuberculosis.

### OBJECTIVES

#### Primary objective

The primary objective of this study is to evaluate the safety profile of MVA85A/AERAS-485 in BCG-Vaccinated, HIV-negative Infants.

#### Secondary objective

The secondary objectives are to:

- To evaluate the efficacy of the MVA85A/AERAS-485 vaccine compared to controls in prevention of tuberculosis using an endpoint derived from epidemiological cohort surveys in BCG vaccinated infants.
- To evaluate the immunogenicity of the MVA85A/AERAS-485 vaccine compared to controls as described by flow cytometric intracellular cytokine staining of CD4 and CD8 T cells producing any of three cytokines (IFN- $\gamma$ , TNF- $\alpha$ , and/or IL-2) after stimulation with a peptide pool of mycobacterial peptides.
- To evaluate the immunogenicity of the MVA85A/AERAS-485 vaccine compared to controls as described by the *ex vivo* ELISPOT test used in previous MVA85A/AERAS-485 human trials.
- To evaluate the immunogenicity of the MVA85A/AERAS-485 vaccine compared to controls as described by the University of Cape Town (UCT) whole blood intracellular cytokine assay.

- To discover correlates of protection from tuberculosis in infants vaccinated with MVA85A/AERAS-485.
- To evaluate the QuantiFERON conversion rate at final study assessment in MVA85A/AERAS-485 recipients compared to controls in subjects without a diagnosis of tuberculosis during the trial.

Exploratory objective: To evaluate the innate immune response to MVA85A/AERAS-485 vaccine in a sequentially-enrolled subset of 100 infants using gene expression and transcriptional profile of blood collected at Study Day 1 as analyzed by microarray analysis.

## DESIGN

This is a Phase II double-blinded randomized controlled evaluation of safety, immunogenicity and efficacy of MVA85A/AERAS-485 in BCG vaccinated infants without tuberculosis or HIV infection. Infants (126 to 182 days) will receive study vaccine (MVA85A/AERAS-485 or *Candida* skin test antigen control). The study is planned at a single site in South Africa but may be executed at more than one site. Enrollment is expected to be completed in 21 months. Given completion of enrollment in 21 months, all infants will be followed for at least 15 months after the last infant is enrolled into the study. The total duration of follow-up for each infant is at least 15 months and up to 39 months. Infants will be followed for the entire duration both for the development of tuberculosis and serious adverse events.

All infants entered into the study will receive a conjugated pneumococcal vaccine (Prevenar®) with the scheduled DPT immunizations Study Day -84 through Study Day -14. On enrollment to the study, eligible infants will be assigned to a study group starting with Study Group 1 and they will be randomly assigned within a study group to receive either MVA85A/AERAS-485 or *Candida* skin test antigen control as shown below. Infants will be assigned to a safety cohort (Study Group 1), then into one of three immunological assay evaluation groups (Study Groups 2-4), and finally the remainder of infants will be assigned into the correlate of protection cohort (Study Group 5). At least 330 infants will be randomized in Study Group 1, up to 50-60 infants each in Study Groups 2-4, and the remaining infants will be randomized in Study Group 5 such that the total number of infants randomized on the study will be 2784.

| Study Group | Cohort Evaluation                | MVA85A/
AERAS-485
(ID) | Control
Candida skin test (ID) | N    |
|-------------|----------------------------------|------------------------------|------------------------------------------|------|
| 1           | Safety (labs and adverse events) | 165                          | 165                                      | 330  |
| 2           | ELISPOT
Immunogenicity        | 30                           | 30                                       | 60   |
| 3           | ICS Assay
Immunogenicity      | 30                           | 30                                       | 60   |
| 4           | Whole Blood
Immunogenicity    | 30                           | 30                                       | 60   |
| 5           | Correlate of
Protection       | 1137                         | 1137                                     | 2274 |
| Total       |                                  | 1392                         | 1392                                     | 2784 |

The sample sizes were selected because they are judged to be adequate for safety evaluations. A sample size of 1392 MVA85A/AERAS-485 subjects will give a greater than 75% chance of observing an adverse event that has an approximately 1 in a 1000 actual rate of occurrence. A sample size of 165 MVA85A/AERAS-485 subjects in the specialized Safety Cohort (Study Group 1) will provide an 80% chance of observing at least one adverse event which has an approximate 1% actual rate of occurrence. Given a tuberculosis cumulative incidence of 3% over 18 months in the control group, 1392 subjects per study group will provide a 90% chance of detecting a 60% reduction between the treated and control groups based on a two-sided log rank test at a significance level of 0.05.

## EVALUATIONS AND FOLLOW-UP

Infants who are randomized at Study Day 0 will be followed up on a regular schedule at Study Day 7 ( $\pm 2$  days), Study Day 28 ( $\pm 5$  days), Study Day 84 ( $\pm 5$  days) and every 84 days ( $\pm 7$  days) thereafter until the end of the study. Specific evaluations at each follow-up will be determined by the study group to which an infant is enrolled. All infants will be followed for adverse events for 28 days after vaccination and for serious adverse events and the development of tuberculosis until the end of the study.

## ANALYSIS OF PRIMARY OBJECTIVE

The safety profile of the treatment groups will be described. Listings will be provided for all subjects with serious adverse events (SAEs). All subjects who receive study vaccine will be included in the analysis and presentation of adverse events; additional analyses for the safety cohort will also be provided to evaluate clinical safety laboratory results. Adverse events will be summarized by treatment group, by study cohort, and for all subjects. Adverse events will also be summarized by severity and by relationship to study vaccine, by treatment group, study cohort, and for all subjects. Adverse events and clinically relevant laboratory results for the safety cohort will be summarized to examine the relationship between treatment group and key safety endpoints including number (percentage) of solicited and spontaneous adverse events, rates of reactogenicity, and number (percentage) of subjects with newly abnormal post-vaccination laboratory values based on predefined neonatal toxicity criteria.

## ANALYSIS OF SECONDARY OBJECTIVES

The number (percentage) of subjects with a diagnosis of tuberculosis based on clinically-derived TB diagnostic criteria will be summarized by treatment group, study cohort, and for all subjects. The cumulative person-years incidence of TB and associated 95% confidence intervals during study follow-up will be summarized by treatment group. Comparison of the incidence of TB in each treatment group will be performed using relative risk summaries and corresponding 95% confidence intervals, as appropriate. Time from Study Day 0 to initial TB diagnosis in each treatment group will be examined using the Kaplan-Meier estimate of the survival function; time to diagnosis between the two treatment groups will be explored using the log-rank test or similar methodology based on distributional assumptions.

The immune response of MVA85A/AERAS-485 will be described for subjects in the three immunogenicity cohorts using the *ex vivo* Elispot assay, the whole blood intracellular cytokine assay cohort, or the ICS assay. Response to each assay will be presented at each post-immunization time point, by treatment group, and by study cohort. ICS assay immune response will be expressed as the percentage of CD4 and CD8 T cells producing any one of three cytokines (IFN- $\gamma$ , TNF- $\alpha$ , or IL-2) or any combination of the three cytokines simultaneously after stimulation with a peptide pool of mycobacterial peptides. Immune responses to MVA85A/AERAS-485 will be compared with control using a linear mixed effects model or other regression models as appropriate. Separate models will be prepared for cytokine responses specific to each assay. Data will be transformed prior to analysis as appropriate.

All infants will have PBMC and plasma collected and stored for future studies of MVA85A/AERAS-485-induced immune correlates of protection. The vaccine-induced immune correlates of protection against tuberculosis are not known. We will compare immune responses between infants who developed tuberculosis (n=60-80, estimated) and those who do not develop tuberculosis.

The number (percentage) of QuantiFERON conversions in all study cohorts who do not receive a diagnosis of TB during the study will be summarized by treatment group, study cohort, and for all subjects.

Innate immune response to vaccination will be examined as an exploratory objective in a sequentially-enrolled subset of 100 randomized subjects. Gene expression and transcriptional profiles of blood collected at Study Day 1 post-vaccination will be analyzed using microarray analysis.

## 1 INTRODUCTION

### 1.1 Background

The only currently available tuberculosis vaccine, Bacillus Calmette-Guérin (BCG), is estimated to reduce the risk of tuberculosis in children by about 80% (1). While effective chemotherapy is available, the uncertainties in diagnosis within the affected populations and the expense and toxicity of chemotherapy permit continued morbidity and death. An improved vaccination would have a positive effect on the health of many people.

Heterologous ‘prime–boost immunization’ strategies involve administration of two different vaccines that deliver the same antigen weeks or months apart. This approach has been demonstrated to elicit higher cellular immunity than a single BCG vaccination in several animal disease models (2,3). Given the protective efficacy of BCG in childhood, BCG would ideally be the priming immunization in such a prime–boost strategy.

The University of Oxford has developed a vaccination strategy with BCG as the priming vaccination and MVA85A/AERAS-485 as the boost. MVA85A/AERAS-485 is a recombinant MVA expressing the *Mycobacterium tuberculosis* antigen Ag85A. MVA is modified vaccinia virus Ankara, a highly attenuated strain of vaccinia virus which does not replicate in mammalian cells. Ag85A is an immunodominant secreted antigen that is highly conserved throughout all mycobacterial species. Importantly for BCG priming, Ag85A is present in all strains of BCG and in all strains of environmental mycobacteria sequenced to date (4).

### 1.2 Description of MVA85A/AERAS-485 Vaccine

The MVA85A/AERAS-485 vaccine consists of the attenuated vaccinia virus MVA vector with a 1176 base-pair insert, which is almost the complete tuberculosis gene for Ag85A, with the tissue plasminogen activator (TPA) signal sequence preceding the N terminus and a monoclonal antibody tag (pk) at the C terminus. Expression of the tuberculosis DNA sequence is regulated by the vaccinia P7.5 early/late promoter.

Ag85A is a secreted 32-kDa protein mycobacterial antigen that is found in abundance in culture fluids of *Mycobacterium tuberculosis* (*Mtb*). It is a member of mycolyl transferase complex and is highly immunogenic. It contains several CD4 T cell epitopes and at least one CD8 T cell epitope and protects against *Mtb* challenge in both mice and guinea pigs (5,6). It is known that BCG-vaccinated mice lose immunity against challenge infection as they age. Brooks and colleagues showed that when these animals were vaccinated with the Ag85A in midlife, they regained protection in the lungs comparable to those of young mice with minimal pathological damage. Immunization of inbred mice with DNA encoding the Ag85A induced statistically significant protective immunity against challenge with *Mtb*. Protection was assessed by measuring the amount of live *Mtb* in the lungs (7). The magnitude of protection with the DNA vaccine was 1–1.5 logs more than placebo-vaccinated animals and similar to BCG vaccine. DNA-Ag85A vaccine induced less protection than BCG in a highly-susceptible guinea pig model (8). However, the prime–boost immunization in mice involving

MVA expressing Ag85A resulted in both CD4+ and class I-restricted CD8+ T cell responses and protected these animals against TB. The protection was equivalent to that of traditional BCG vaccination (6). Furthermore, MVA85A/AERAS-485 in humans significantly boosted BCG-primed anti-TB immunity after it was given to 31 adult volunteers and produced levels of antigen-specific IFN- $\gamma$ -secreting T cells 5–30 times higher than in people given a BCG vaccination (9). Ag85A is an important protective antigen.

### 1.3 Non-clinical Experience with MVA85A/AERAS-485

Protective efficacy studies using a BCG prime-MVA85A/AERAS-485 boost strategy, followed by *Mtb* challenge, have been conducted in 4 animal species (mice, guinea pigs, non-human primates and cattle). These experiments suggested improved protection of the combination compared to BCG alone.

The toxicity of MVA85A/AERAS-485 was tested in mice following 2 ID injections of  $1 \times 10^7$  pfu MVA85A/AERAS-485 over 15 days. Control animals received PBS. The mice were sacrificed 14 days after the second dose. MVA85A/AERAS-485-injected mice showed no differences from PBS-injected control animals in body weight, organ weight, histopathology, or haematological and biochemical parameters. A low level of local irritation at the site of administration was observed with MVA85A/AERAS-485.

### 1.4 Clinical Experience with MVA85A/AERAS-485

A total of 13 clinical studies (11 Phase I, 2 Phase II) of MVA85A/AERAS-485 have been completed or are ongoing. A total of 102 healthy adults have received MVA85A/AERAS-485 in the completed studies, and 200 subjects (66 adults, 12 adolescents, 24 children, 98 infants) have been vaccinated in the ongoing studies. The doses of MVA85A/AERAS-485 in these studies range from  $1 \times 10^7$  to  $1 \times 10^8$  pfu.

MVA85A/AERAS-485 induced high levels of antigen-specific IFN- $\gamma$  secreting T cells in BCG-naïve adults, and even higher levels in adults previously vaccinated with BCG either 1 month previously or 1-20 years previously. Immunogenicity of MVA85A/AERAS-485 in BCG-vaccinated adolescents and adults latently infected with *Mtb* was similar to that seen for BCG-vaccinated healthy adults. In BCG-vaccinated infants, induction of measurable levels of antigen-specific T cells was observed, with similar results seen when MVA85A/AERAS-485 was given either on its own or concomitantly with EPI vaccines.

Over 300 individuals have received MVA85A/AERAS-485 in clinical trials to date, including BCG-naïve adults; BCG-vaccinated adults, adolescents, children, and infants; HIV positive adults and adults latently infected with *Mtb*. Final safety data are available for 129 of these subjects. No serious adverse events judged to be related to MVA85A/AERAS-485 have been reported in these subjects. The safety profile of MVA85A/AERAS-485 developed so far consists of local adverse events in most subjects. Although there were some severe local reactions such as erythema, swelling, and pain at the injection site, most local reactions were typically mild in severity and most resolved within 1 week of vaccination. Less frequent systemic reactions included constitutional manifestations resembling flu such as fever, headache, rash, malaise, fatigue, anorexia, cough, arthralgia, and myalgia. These systemic

events were also usually mild and all spontaneously resolved within 24-48 hours after vaccination.

## 1.5 Rationale

The available live tuberculosis vaccine, BCG provides incomplete protection against pulmonary tuberculosis. Due to natural inhibition of a second dose, a BCG revaccination does not provide much additional protection. MVA85A/AERAS-485 presents a tuberculosis antigen in the setting of a live but non-replicating virus vaccine to increase T-cell immunity and thus protection against tuberculosis. MVA85A/AERAS-485 has been administered to over 300 humans without any vaccine-related serious adverse effects and shows evidence of immunogenicity. This study will evaluate the safety and immunogenicity of MVA85A/AERAS-485 in BCG vaccinated infants and has the potential to demonstrate the ability of the vaccine to prevent tuberculosis.

## 2 STUDY OBJECTIVES and DESIGN

### 2.1 Objectives

#### Primary objective

The primary objective of this study is to evaluate the safety profile of MVA85A/AERAS-485 in BCG-vaccinated, HIV-negative infants.

#### Secondary objective

The secondary objectives are:

- To evaluate the efficacy of the MVA85A/AERAS-485 vaccine compared to controls in prevention of tuberculosis using an endpoint derived from epidemiological cohort surveys in BCG vaccinated infants.
- To evaluate the immunogenicity of the MVA85A/AERAS-485 vaccine compared to controls as described by flow cytometric intracellular cytokine staining of CD4 and CD8 T cells producing any of three cytokines (IFN- $\gamma$ , TNF- $\alpha$ , and/or IL-2) after stimulation with a peptide pool of mycobacterial peptides.
- To evaluate the immunogenicity of the MVA85A/AERAS-485 vaccine compared to controls as described by the *ex vivo* ELISPOT test used in previous MVA85A/AERAS-485 human trials.
- To evaluate the immunogenicity of the MVA85A/AERAS-485 vaccine compared to controls as described by the UCT whole blood intracellular cytokine assay.
- To discover correlates of protection from tuberculosis in infants vaccinated with MVA85A/AERAS-485.

- To evaluate the QuantiFERON conversion rate at final study assessment in MVA85A/AERAS-485 recipients compared to controls, in infants without a diagnosis of tuberculosis during the trial.

Exploratory objective: To evaluate the innate immune response to MVA85A/AERAS-485 vaccine in a sequentially-enrolled subset of 100 infants using gene expression and transcriptional profile of blood collected at Study Day 1 as analyzed by microarray analysis.

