| Blood volume (mL) per visit   |                  | 6                | 8               |     |     | 8   |     |

a Written informed consent must be obtained prior to initiation of study screening activities and may be obtained prior to Day -84. Medical history/physical exams and blood collection for HIV-1 and QuantiFERON testing must be completed within 35 days prior to Study Day 0; blood collections for baseline immunology must be completed within 7 days prior to randomization.

After study day 84 study enrollees will be visited by a study member at least every 84 days until the end of the study. At these visits, infants will be weighed, assessed for the occurrence of a new SAE, and assessed for admission to a case verification ward for suspected tuberculosis. Any infant with a cohabiting household member in which the diagnosis of tuberculosis has been made or any infant that has 1) weight loss in last two months, 2) cough for more than two weeks without improvement, 3) failure-to-thrive, or 4) conversion to a positive QuantiFERON test or positive Mantoux test will be admitted to the case verification ward for diagnosis of tuberculosis.

A QuantiFERON test will be drawn on Study Day 336 for all subjects followed to Study Day 336 and on the last clinic visit in all infants without the clinical diagnosis of tuberculosis. Follow up of all infants will be terminated at the next scheduled study visit after the last enrollee completes 15 months of follow-up (Study Day 420).

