#### **3.5.2 Clinical Assessments and Laboratory Tests**

An examination of the injection site and draining lymph nodes of injection arm will be performed 60 minutes after study vaccine/control administration and at Study Days 7 and 28. Infants will have vital signs recorded at Study Days 7, 28, and 84. Infants will also have their weight recorded prior to vaccination on Study Day 0 and then again on Study Day 7, 28, 84 and every 84 days thereafter.

Laboratory evaluations are planned for only the infants enrolled in the Safety Cohort (Study Group 1). The Safety Monitoring Committee may determine that additional infants need to enroll in this cohort after a review of the safety data from these infants. Blood for hematology and serum chemistry will be collected at screening and on Study Days 7 and 28. All laboratory samples will be processed according to SOPs provided by the local clinical laboratory.

Prior to any blood draw, all infants will be evaluated for clinical signs of anemia (e.g., palmar pallor). If the evaluation suggests anemia in an infant, the infant will have hemoglobin evaluated by fingerprick. If the hemoglobin obtained by fingerprick is  $< 9\text{g/dL}$ , then blood will not be drawn from that infant at that visit.

All infants randomized to the study will have blood for QFT-G collected during screening, again on Study Day 336, during evaluations for TB in the CV ward, and on the last scheduled visit for each infant.

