#### TB Case Definition Endpoint #1

Any of the following numerical categories

1. Isolation of *M. tuberculosis* from any site.
2. Identification of *M. tuberculosis* by an approved molecular diagnostic technique from any site.
3. Histopathology diagnostic for tuberculosis disease (such as caseating granulomas)

4. Choroidal tubercle diagnosed by an ophthalmologist
5. Miliary pattern on chest X ray in a HIV negative infant
6. Clinical diagnosis of tuberculous meningitis (CSF protein >0.6 g/L and pleocytosis >50/mm^3 with mononuclear cell >50%) with features of basal meningeal enhancement and hydrocephalus on head CT.
7. Vertebral spondylosis
8. A single smear/histology specimen positive for acid fast (or auramine positive) bacilli from a normally sterile body site.
9. One of the following:
  - a) Two acid fast or auramine smears positive each from a separate collection morphologically consistent with mycobacteria from either sputum or gastric aspirate that are not found to be non-tuberculous mycobacteria bacteria on culture , OR
  - b) QuantiFERON conversion from negative or indeterminate to positive, OR
  - c) Tuberculin skin test  $\geq 15$  mm

AND

One of the following compatible radiographic features:

- a) Calcified Ghon focus, OR
- b) Pulmonary cavity, OR
- c) Hilar/mediastinal adenopathy, OR
- d) Pleural effusion, OR
- e) Airspace opacification,

AND

One of the following clinical manifestations:

- a) Cough without improvement for longer than two weeks, OR
- b) Weight loss of at least 10% of body weight for at least 2 months, OR
- c) Failure to thrive (crossing at least one entire major centile band downward) for at least 2 months, where the major centile bands are defined as <97th–90th, <90th–75th, <75th–50th, <50th–25th, <25th–10th, and <10th–3rd weight-for-age centiles\*.

*\*Centers for Disease Control (CDC) Growth Charts (USA), developed by the National Center for Health Statistics in collaboration with the National Center for Chronic Disease Prevention and Health Promotion (2000).*

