## **7.6 Sample Size Considerations**

The sample sizes were selected because they are judged to be adequate for safety evaluations. A sample size of 1392 MVA85A/AERAS-485 subjects will give a greater than 75% chance of observing an adverse event that has an approximately 1 in a 1000 actual rate of occurrence. A sample size of 165 MVA85A/AERAS-485 subjects in the safety cohort will provide an 80% chance of observing at least one adverse event which has an approximate 1% actual rate of

occurrence. Given a tuberculosis cumulative incidence of 3% over 18 months in the control group, 1392 subjects per treatment group (2784 subjects total) would be required to demonstrate positive efficacy when the true efficacy of MVA85A/AERAS-485 is approximately 60%. An estimate of 7.5% of subjects lost to follow-up in each treatment group is assumed over 18 months. Calculations are based on a two-sided log-rank test at a significance level of 0.05. Calculations assume 90% power to detect a 60% reduction in tuberculosis rate between the MVA85A/AERAS-485 and control groups; given an estimated enrollment over 21 months, the last subject to enroll in the study will be followed for a minimum of 15 months to maintain statistical power.

However, delays in recruitment and/or a lower TB incidence may result in a need to extend follow-up to preserve the power of the study to detect a treatment group difference. To assess the possible impact of departures from planned subject recruitment rate, total number of TB cases accrued, loss to follow-up, or proportional hazards assumptions, an independent statistician not involved with the conduct or analyses of the trial will perform a sample size review using an interim pooled estimate of the TB event rate and the original treatment effect. It is critical that this interim review occur when sufficient TB events have accrued, to allow for a stable estimate, but before the total cohort has been recruited, due to trial management issues. The initial sample size review is proposed to occur while enrollment is ongoing but when approximately 30% of expected events have accrued, but no later than before 75 percent of the total cohort has been recruited. Details of this review and analysis will be documented in a statistical analysis plan, finalized prior to the review, and in the SMC charter. Timing of subsequent reviews will be determined based on planned completion of recruitment closure after 21 months and enrollment rate.

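### The stated QuantiFERON objective compares arms only among infants who stayed free of TB, a post-randomisation subset, and does not match the unrestricted summaries in Section 7.4.5

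*Protocol*

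**What the plan says.** The last secondary objective in Section 2.1 evaluates QuantiFERON conversion at the final study assessment in vaccine recipients "compared to controls, in infants without a diagnosis of tuberculosis during the trial". The Abstract states the same objective, and its analysis paragraph keeps the restriction: "The number (percentage) of QuantiFERON conversions in all study cohorts who do not receive a diagnosis of TB during the study will be summarized". The breakdown there is by arm and by cohort.

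Section 7.4.5 is wider. It summarises positive results at Day 0, Day 336 and the last visit by treatment group. It cross-tabulates negative-to-positive conversion by treatment group with no exclusion of TB cases. It also reports conversion separately for infants with and without TB, in the safety population.

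The sampling rules disagree about the last visit. Section 3.1 draws the test at Day 336 in all infants followed that far and "on the last clinic visit in all infants without the clinical diagnosis of tuberculosis". Section 3.5.2 says that all randomised infants are tested at screening, "again on Study Day 336, during evaluations for TB in the CV ward, and on the last scheduled visit for each infant".

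In Section 7.3.1, one of the evidence-of-infection criteria in category 9 of TB Endpoint #1 is "QuantiFERON conversion from negative or indeterminate to positive". Endpoint #2 has the same criterion.

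**The concern.** Being free of TB at the end of the trial is an outcome. It is the outcome the vaccine is meant to improve, and infected infants are the ones at risk of losing that status. Conversion also leads to removal from the subset by design: it triggers admission to the case verification ward (Sections 3.1 and 3.5.6) and can count towards the case definition.

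Suppose the vaccine reduces TB by stopping infected infants from progressing. Infected control infants who progress are diagnosed and dropped. Their vaccinated counterparts stay well and remain in the subset as converters. The vaccine arm then shows more conversions even though infection was equal. A real but modest effect on infection could be hidden in the same way. The reader of the final report would not know whether the ratio reflected infection or selection.

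**Working it through.** **The plan's own figure.** Section 7.6 gives the TB assumptions used here: "Given a tuberculosis cumulative incidence of 3% over 18 months in the control group", 1392 infants per arm, and "Calculations assume 90% power to detect a 60% reduction in tuberculosis rate between the MVA85A/AERAS-485 and control groups". "Calculations are based on a two-sided log-rank test at a significance level of 0.05". A 60% reduction from 3.0% is 1.2%. The hazard ratio is ln(1 − 0.012)/ln(1 − 0.03) = 0.396. Freedman's formula gives 57 events, and 57/(0.030 + 0.012) = 1358 per arm before losses. Taking half of the assumed 7.5% loss as the average gives 1358/(1 − 0.0375) = 1411. At 1392 per arm with that half-loss, power is 90.0%. The TB planning figures are therefore coherent. The protocol gives no expected rate, sample size or power for QuantiFERON conversion.

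**Conversion in the TB-free subset.** Let q be the proportion of all infants in an arm who convert, p the proportion with TB, and s the share of TB cases who are converters. Then

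subset rate = (q − s·p)/(1 − p).

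The values p = 0.030 (control) and 0.012 (vaccine) come from Section 7.6. The values of q and s are assumptions, because the document gives neither.

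**Vaccine affects progression only (q equal in both arms, true ratio 1.00).**

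| q | s | Control | Vaccine | Subset ratio |
|---|---|---|---|---|
| 6% | 1 | 0.030/0.97 = 3.09% | 0.048/0.988 = 4.86% | 1.57 |
| 10% | 1 | 0.070/0.97 = 7.22% | 0.088/0.988 = 8.91% | 1.23 |
| 15% | 1 | 0.120/0.97 = 12.37% | 0.138/0.988 = 13.97% | 1.13 |
| 20% | 1 | 0.170/0.97 = 17.53% | 0.188/0.988 = 19.03% | 1.09 |
| 10% | 0.5 | 0.085/0.97 = 8.76% | 0.094/0.988 = 9.51% | 1.09 |
| 20% | 0.5 | 0.185/0.97 = 19.07% | 0.194/0.988 = 19.64% | 1.03 |

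**Masking.** At q = 10% in control and s = 1, the control subset rate is 7.22%. The vaccine arm shows the same subset rate when its overall conversion is 0.0722 × 0.988 + 0.012 = 8.33%. A true 17% reduction in infection would then appear as no difference.

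**Vaccine affects infection only.** With 60% fewer infections, the same risk of TB once infected, and s = 1, conversion at q = 10% is 10% against 4%. The subset rates are 7.22% and (0.04 − 0.012)/0.988 = 2.83%, ratio 0.39, close to the true 0.40. There is no reversal.

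**All infants, TB cases kept.** Under the progression-only scenario the ratio is q/q = 1.00 at every q and s.

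**The case against.** The strongest reply is that Section 7.4.5 is the operative analysis section and does not impose the restriction. It already plans an unrestricted by-arm cross-tabulation and a split by TB status. This stands. A reader of the objective alone might infer that conversion is compared only among TB-free infants, and that is not so. What remains is a mismatch: the objective and the Abstract name one analysis set, and 7.4.5 tabulates more than that.

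A reader might also infer that an effective vaccine will appear to increase infection. The documents do not support that. The reversal requires the vaccine to act more on progression than on infection, and its size depends on how many TB cases are converters. Categories 1 to 8 of Endpoint #1, and the smear and skin-test options in category 9, need no QuantiFERON conversion, so s = 1 is the extreme case.

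Finally, conversion is only to be summarised. No test, interval or decision rule is attached to it. With 1392 × 0.925 = 1288 infants per arm, a two-sided 5% comparison of proportions at 10% infection would come out significantly against the vaccine about 35% of the time at s = 1 and about 10% at s = 0.5. These figures describe a test the protocol does not plan and are illustrative only.

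The reply does not dispose of the sampling conflict. Under Section 3.1, infants with clinical TB have no last-visit result, so an all-infant comparison at the final assessment could not be completed however the analysis is worded.

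**Conclusion.** The point holds in limited form. The stated objective and the Abstract analysis condition on a post-randomisation outcome that the vaccine is meant to change and that conversion helps to define, and they do not match Section 7.4.5. If the vaccine acts mainly on progression, the restricted ratio is biased against it. Under the protocol's TB rates and equal infection, it runs from 1.09 at 20% infection to 1.57 at 6% if all TB cases are converters. At 10% infection it is 1.23 if all are converters and 1.09 if half are. If the vaccine acts by preventing infection, the ratio is not reversed. The infection rate, the share of converters and the mechanism are all assumptions. This is one secondary objective, reported descriptively. The primary safety objective and the TB efficacy analysis are unaffected. It should be corrected, but it does not threaten the trial.

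**What to change.** - Reword the objective in Section 2.1 and the Abstract, and the Abstract's analysis paragraph, to match Section 7.4.5. The main between-arm comparison should be conversion among all randomised, vaccinated, baseline QuantiFERON-negative infants, whether or not TB was diagnosed, using the scheduled Day 336 and final-visit tests.
- Add case-verification-ward tests as a sensitivity analysis, not in the main comparison. Ward admission follows symptoms, household contact or a positive test, so the number of chances to be found positive may differ by arm. In the progression scenario that would favour the vaccine.
- Keep the TB-free subset as descriptive only.
- Reconcile Section 3.1 with Section 3.5.2 so that infants with TB also have a final-visit result.

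The cost is small. Section 3.5.2 already provides for the samples. If Section 3.1 has been followed, the extra tests are those in TB cases: under the planning rates and before losses, about 0.030 × 1392 = 42 control and 0.012 × 1392 = 17 vaccine infants. The drawback is that some of these results will be obtained after TB treatment, which should be noted when they are reported.
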